##### Non-participation analysis

The baseline measures of the participants of the study will be compared to those of non-participants using chi-squared statistic for categorical variables and analysis of variance for continuous variables.

##### Compliance

Compliance will be analysed by descriptive statistics. Additional analyses will be carried out in which data relating to compliance with the program elements is taken into account. To this end, we will determine whether the level of compliance (based number of log-ins and self-reported use data) is significantly associated with the changes over time in primary and secondary outcome measures.

##### Patients’ evaluation of the intervention program

Descriptive statistics will be generated to describe the intervention and control groups in terms of patients’ evaluation of the intervention program. Outcomes will be compared using analysis of variance.

##### Cost effectiveness

The outcome of the cost-effectiveness analysis is the incremental cost-effectiveness ratio, expressed in cost / QALY, represents the additional costs required for the particular intervention to generate one additional QALY in comparison to doing nothing. These are calculated as follows:

ICER = (Costs of the intervention group – costs of the UC group) /

(QALYs of the intervention group – QALYs of the UC group)

Secondly, the ICER will be expressed in cost/MET minutes MVPA/week, representing the additional costs required for the gain in PA level/week.

State of the art health economic methods will be applied. These include the estimation of the degree of uncertainty about each input parameter and the use of probabilistic sensitivity analyses. Parameter values will be drawn randomly from the assigned distributions, using Monte Carlo simulation with 10,000 iterations. The degree of uncertainty will be illustrated by using confidence intervals for costs and health effects. Scatter-plots, confidence ellipses on cost-effectiveness planes and cost-effectiveness acceptability curves will be presented [57]. As an indication of whether an intervention will be considered cost-effective the ICER is compared to a range of ceiling ratios varying from €20 k / QALY for prevention to €80 k / QALY for severe diseases, in the Netherlands. If necessary, Value of Information (VOI) analysis will be performed to support decision-making regarding adoption and further research [58].

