## Methods/Design

### Trial design

The PABLO study is a three-armed multicenter randomised controlled trial (RCT). The participants will be recruited from a specialized cancer hospital: the Netherlands Cancer Institute (NKI), Amsterdam, and a large teaching hospital: Rijnstate, Arnhem.

Participants will be randomised to one of the three study arms. Participants allocated to the first intervention arm will receive 6-month access to the intervention (IPAS). The second intervention arm will receive 6-month access to IPAS, as well as additional support by a monthly phone call with a physiotherapist (IPAS+TS). The control group will receive usual care and a leaflet with PA guidelines. The total study duration per participant is 12 months. This protocol will follow the SPIRIT guidelines. Figure 1 contains the flowchart for the study.

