### Aim and hypotheses

The primary aim of the study is to evaluate the effectiveness of the IPAS program (with or without additional telephone support), compared to usual care, on objectively measured PA in patients with primary breast and prostate cancer who have completed primary treatment 3–12 months ago.

We have the following secondary aims: first, to evaluate the effect of the two interventions on self-reported PA, stage of change (regarding PA behaviour), fatigue, mood and health related quality of life compared to usual care. Second, to perform a cost-effectiveness analysis to estimate the expected allocative efficiency of IPAS and IPAS+TS vs. usual care. Third, to identify potential moderators (clinical and socio-demographic characteristics) and mediators (attitudes towards PA, social support and self-efficacy) of the intervention effect on PA levels. Finally, as an exploratory aim (as the study is not powered for this comparison), to evaluate the comparative effect of IPAS alone with IPAS+TS on objectively measured PA.

We hypothesize that using IPAS or IPAS+TS will increase levels of PA more than usual care where patients only receive a leaflet with current PA guidelines. Additionally, several studies have shown the value of personal feedback to increase cancer survivors’ PA levels [20–22]. Therefore, we hypothesize that participants in the IPAS+TS group will increase their PA-levels to a greater extent than participants receiving IPAS only. Additionally, we hypothesize that increased PA resulting from the exposure to IPAS or IPAS+TS will lead to decreased levels of fatigue, and improved HRQOL and mood as compared to control. Finally, we hypothesize that total costs for IPAS will be lowest compared to IPAS+TS, due to the low intervention costs, or somewhat higher compared to UC, and “gains” for IPAS−/+TS in terms of improved QoL.

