##### Cost effectiveness analysis

A cost-effectiveness analysis (CEA) will be performed comparing internet-based PA programs versus usual care, from a societal perspective for both breast cancer and prostate cancer. Two Markov decision models will therefore be constructed with mutually exclusive health states. The model will simulate the course of events in a breast and prostate cancer cohort, based on the PABLO data for comparing the two intervention strategies and compared to usual care. The models will first evaluate the cost-effectiveness using the time horizon of the study (12 months), and subsequently will simulate the expected costs and outcome with a lifetime horizon.

The cost-effectiveness of the internet-based PA programs versus usual care will be expressed as: [1] the effectiveness part of the equation will be based on EQ5D scores after 6 and 12 month follow-up. [2] the cost part of the equation will be expressed in the following items:

Direct costs: The intervention costs will be calculated, including health professional labour (including time spent on treatment per patient by social workers by means of the Activity Based Costing (ABC) method) [50], staff training, administration, and material costs (e.g. related to information technology). Costs of personnel involved in the interventions will be calculated by the time they are involved times the standard costs for (para)medical personnel. By means of the iMCQ, all patients will be asked to report on T1 and T2 about their use of health care services (e.g., GP, medical specialist, paramedical care etc.), prescribed medication use. Direct non-medical costs will include travel costs.

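### The ICER and its comparison with the cost-per-QALY ceilings are defined only against usual care, although the trial has three alternative strategies and the plan foresees comparing the two interventions.

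*Protocol article*

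**What the plan says.** The Trial design section states that "The PABLO study is a three-armed multicenter randomised controlled trial (RCT"). The section on IPAS with telephone support describes the second intervention arm as IPAS plus monthly physiotherapist support.

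The economic aim, in Aim and hypotheses, is "to perform a cost-effectiveness analysis to estimate the expected allocative efficiency of IPAS and IPAS+TS vs. usual care". The same section gives the expected cost ordering: "we hypothesize that total costs for IPAS will be lowest compared to IPAS+TS, due to the low intervention costs".

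The Cost effectiveness paragraph of the Statistical analysis section defines the ICER in words: it "represents the additional costs required for the particular intervention to generate one additional QALY in comparison to doing nothing". It then gives one formula, with numerator "Costs of the intervention group – costs of the UC group" and denominator "QALYs of the intervention group – QALYs of the UC group". As an indication of cost-effectiveness, the ICER is compared with ceilings from EUR 20k to EUR 80k per QALY.

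The Cost effectiveness analysis section, under Other outcomes, says that the Markov models are "for comparing the two intervention strategies and compared to usual care". No ICER or criterion is attached to the comparison of the two interventions.

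**The concern.** A payer choosing among three alternatives has to judge each step up in cost against the next-cheaper option still in contention. A ratio against usual care answers a different question: whether IPAS+TS would be worth having if IPAS did not exist. Because IPAS+TS contains IPAS, that ratio credits the combined programme with any benefit the website alone already delivers at lower cost.

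IPAS+TS could therefore fall under a ceiling while the physiotherapist component, taken by itself, does not. The Background names exploring the added value of that support as an aim, and the Discussion lists the head-to-head comparison as a strength. The printed ICER cannot inform either.

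**Working it through.** **Inputs.** From the protocol: three strategies, one ICER formula against usual care (UC), ceilings of EUR 20k and 80k per QALY, and the hypothesis that IPAS costs less than IPAS+TS. The protocol states no cost, QALY or ICER, so there is no figure to reproduce. All costs and QALYs below are assumptions.

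**Formulas.** Let c_I, q_I be the extra cost and QALYs of IPAS against UC, and c_T, q_T those of IPAS+TS against UC.
- Plan's ICER of IPAS+TS: c_T / q_T
- Increment over IPAS: (c_T − c_I) / (q_T − q_I)
- Net monetary benefit against UC at ceiling λ: λ·q − c

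**Relation between the two ratios.** When 0 < q_I < q_T,

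c_T / q_T = [q_I · (c_I / q_I) + (q_T − q_I) · (increment over IPAS)] / q_T.

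The plan's ratio is thus a QALY-weighted average of the first step (UC to IPAS) and the second (IPAS to IPAS+TS). If the first step is the better value, the average always lies below the second step.

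**Numbers.** Hold IPAS at +EUR 100 and +0.020 QALY, so its ICER against UC is 100 / 0.020 = EUR 5,000 per QALY, and vary IPAS+TS:

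| IPAS+TS v UC | ICER v UC | ICER v IPAS |
|---|---|---|
| +500, +0.030 | 500/0.030 = 16,667 | 400/0.010 = 40,000 |
| +300, +0.022 | 300/0.022 = 13,636 | 200/0.002 = 100,000 |
| +500, +0.019 | 500/0.019 = 26,316 | dominated (400 dearer, 0.001 QALY fewer) |
| +500, +0.040 | 500/0.040 = 12,500 | 400/0.020 = 20,000 |

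Check of the identity on row 1: (0.020 × 5,000 + 0.010 × 40,000) / 0.030 = 500 / 0.030 = 16,667.

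**Reading the rows.**
- Row 1: IPAS+TS passes EUR 20k against UC, but its increment does not. At λ = 20k, net benefit is 20,000 × 0.020 − 100 = EUR 300 for IPAS and 20,000 × 0.030 − 500 = EUR 100 for IPAS+TS, so IPAS is preferred. At λ = 80k the figures are EUR 1,500 and EUR 1,900, so IPAS+TS is preferred and there is no reversal.
- Row 2: passes both ceilings against UC; the increment fails both.
- Row 3: fails EUR 20k but passes EUR 80k against UC, although IPAS is cheaper and yields more QALYs.
- Row 4: both ratios are at or under EUR 20k, so no reversal.

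**The case against.** The strongest reply is that the comparison is not missing. The Cost effectiveness analysis section foresees it, the models yield costs and QALYs for every arm, and nothing confines the acceptability curves to pairs against usual care. This stands: a reader might infer that the plan leaves out IPAS against IPAS+TS altogether, and the document does not support that. What remains is that the only ICER defined, and the only ratio set against the ceilings, excludes it. The general commitment to current health-economic methods does not close the gap, because the text spells it out as parameter uncertainty and probabilistic sensitivity analysis, neither of which changes the comparator.

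Second, the formula fits the stated economic aim, and the head-to-head comparison on objectively measured activity is labelled exploratory for lack of power. That is correct, but it concerns the activity outcome. The economic analysis carries uncertainty through simulation and can do so for this contrast too.

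Third, ordering and dominance rules normally sit in a fuller health-economic plan, and their absence from an article is no fault. This is fair as far as it goes; the point rests on the formula that is printed, not on the missing detail.

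Fourth, the ceilings are offered only as an indication, so no text says to adopt IPAS+TS because its ratio against usual care passes. This stands too.

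Fifth, IPAS need not be the right comparator. That it is cheaper is a hypothesis, and the perspective is societal, with productivity losses included, so total costs may not follow intervention costs. If IPAS proves dominated or extendedly dominated, usual care is the correct comparator for IPAS+TS. This stands and shapes the fix.

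A reader might also make something of the reference to doing nothing, or of the costing text "time spent on treatment per patient by social workers" when physiotherapists deliver the added component. The formula names usual care, and the next costing sentence covers all personnel involved in the interventions. These are clerical corrections and carry no weight here.

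**Conclusion.** The point holds as a mismatch between a usual-care-only ICER and a three-option decision that the same protocol foresees. If IPAS is cheaper than IPAS+TS and is the better-value first step, the defined ratio understates the cost per QALY of adding physiotherapist support. Under the assumed inputs the contrast runs from 12,500 against 20,000 (no reversal), through 16,667 against 40,000, to 13,636 against 100,000 and to outright dominance.

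It would go too far to conclude that the plan will lead to a wrong adoption decision. Whether a reversal occurs depends on costs and QALYs that the protocol does not give and on which ceiling in the range is applied. The primary activity analysis and the sample size are unaffected.

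**What to change.** Reconcile the Cost effectiveness paragraph of the Statistical analysis section with the Cost effectiveness analysis section:

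- Keep the ICERs of IPAS and IPAS+TS against usual care.
- Add a full incremental analysis: order the three strategies by total societal cost, remove dominated and extendedly dominated ones, and report each remaining ICER against the next-cheaper strategy, whichever that proves to be.
- Present net monetary benefit and acceptability curves for all three strategies together, from the same simulations.
- As clerical edits, name the comparator as usual care plus leaflet and correct the staff group in the costing sentence.

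The cost is a few sentences of text. The analysis uses the same model outputs and simulations and needs no new data.

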## Discussion

Meeting PA guidelines is important for the wellbeing of cancer survivors and is associated with considerably lower health care spending. The aim of this trial is to evaluate the (cost)effectiveness of the IPAS intervention alone or combined with physiotherapy counselling on PA levels of breast and prostate cancer survivors compared to usual care. This intervention could have important implications for the health and well-being of a large number of cancer survivors, as prostate and breast cancer are the most frequent occurring types of cancer.

This study has limitations that need to be acknowledged. The first is related to the interventions, neither of which is supervised in-person. A recent meta-analysis of individual patient data of 34 exercise RCTs has shown that such supervised interventions are more effective than unsupervised interventions in terms of quality of life and physical functioning [59]. However, since long-term maintenance of PA is necessary to optimally benefit from physical activity, providing supervised interventions is financially and practically undesirable. In the IPAS-TS intervention we offer a partly supervised intervention which could be characterized as guided self-management. The second limitation is that we will not reach every single cancer survivor, especially those that are most in need. Chances are that -given the nature of the intervention- we will not be able to recruit older, less educated, less motivated or less tech-savvy patients, whereas many of these patients may benefit most from improving their PA level. We anticipate that our non-participant analysis will help us clearly define the characteristics of these patients and will provide leads to better target these patients in future exercise programs. A third limitation may be that the internet-based intervention is prone to suffer from relatively high attrition rates, which is a common observation with internet-based behavioral interventions [60]. We anticipate that, by adding remote supervision, the compliance and the efficacy of the intervention will increase substantially. A further limitation may be that we did not chose for a forced 50–50% inclusion rate of breast and prostate cancer survivors. Since we do not expect significant differences in our outcome measures within breast and prostate cancer survivors, we use stratification on tumor type to level out possible differences. Although the degree of (in) activity is a selection criteria, it is known in behavourial studies that wide attention for healthy behaviour, can also influence the PA levels of control group patients. This “moving target” effect is difficult to anticipate on in methodological terms, but should be taken into account from the onset.

The proposed study also has several strengths, including: [1] using the IPAS intervention which was already piloted, [2] the large sample size, [3] the multicenter RCT design, [4] the intention to treat approach, [4] a relatively long term follow-up, [5] using objectively measured PA as outcome, [6] the addition of a cost-effectiveness analysis, [7] a head to head comparison of an online-only versus a partly remotely supervised program 8] a detailed analysis of the background characteristics of those who decline participation in the trial [9] targeting breast and prostate cancer survivors that have a high prevalence, [10] detailed analyses of psychological factors that may predict long-term physical activity behaviour.

In summary, we here presented the rationale and design of the PABLO trial which aims to improve PA levels of breast and prostate cancer survivors via internet-based or a minimally supervised intervention. The trial adds to the literature in several important ways (eg. cost effectiveness analysis, non-participant analysis). If proven to be (cost)effective, these interventions may be added to the standard care of breast and prostate cancer survivors to enhance their health and quality of life in a modern and efficient way.

## Abbreviations

(S)AE: (Serious) Adverse Event
ABC: Activity Based Costing
CEA: Cost-Effectiveness Analysis
GPS: Global Positioning System
HRQOL: Health Related Quality of Life
ICER: Incremental Cost Effectiveness Rate
iMCQ: Medical Consumption Questionnaire
IPAQ: International PA Questionnaire
IPAS: Internet Based Physical Activity Support
IPAS+TS: Internet Based Physical Activity Support + Telephone Support
iPCQ: Productivity Cost Questionnaire
IRB: Institutional Review Board
MET: Metabolic Equivalent Time
MFI: Multidimensional Fatigue Inventory
MVPA: Moderate to Vigorous Physical Activity
NKI: The Netherlands Cancer Institute
PA: Physical Activity
POMS: Profile Of Mood States
QALY: Quality Adjusted Life Year
RCT: Randomised Controlled Trial
SAE: Serious Adverse Event
SCT: Social Cognitive theory
SF-36: Medical Outcomes Study Short Form-36
TPB: Theory of Planned Behaviour
TTM: Transtheoretical Model
UC: Usual Care
WMO: Wet Medisch- Wetenschappelijk onderzoek Dutch law of scientific research involving human subject
